### Criteria for discontinuing or modifying allocated interventions {11b}

Participants can leave the trial at any time for any reason if they wish to do so without any consequences. The participant’s participation in this trial can also be ended by the investigator if the participant is uncooperative and/or does not attend study visits. The participant’s data that have been collected up to that moment will be included in the analysis. This trial will be prematurely ended in case of any abundance in adverse events or procedure/compound-related complications or if the independent physician advises this termination. Criteria for trial termination include any suspected unexpected serious adverse event (SAE) based on an allergic reaction and clear allergic or iatrogenic effects in two or more participants.

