### Sample size {14}

A sample size of 173 participants was calculated to provide 80% power to detect a common odds ratio (indicating the odds of improvement of 1 point on the mRS) of 6.02 in the distribution of scores on the mRS at 90 days between the treatment and control groups with a two-sided significance level of 0.05, assuming a similar between-group distribution of the mRS as in a recent AIS trial [11]. Taking into account of possible protocol violations and dropouts, we intend to enroll 220 participants (110 per group).

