## Statistical methods

### Statistical methods for primary and secondary outcomes {20a}

The primary outcome will be analyzed by fitting a proportional-odds logistic-regression model to calculate the common odds ratio as a measure of the likelihood that the treatment group will lead to lower mRS scores than the control group (shift analysis).

For secondary outcomes, categorical variables will be compared with chi-square test or Fisher exact test. Longitudinal continuous variables will be analyzed by fitting a repeated-measures analysis model. Additionally, adverse events, serious adverse events, and laboratory abnormalities will also be compared using the chi-square test or Fisher exact test as appropriate.

All analyses will be performed in the intention-to-treat population using SAS version 9.4 (SAS Institute Inc). *P* values of less than 0.05 will be considered statistical significance, and all tests will be two-sided. No adjustments will be made for multiple comparisons.

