### Adverse event reporting and harms {22}

All adverse events reported by the participants or observed by the investigators will be recorded. Adverse events will begin to be collected after the participant has provided consent and enrolled in the trial. An adverse event is recorded at any time. When an adverse event occurs, it is recorded immediately. If a participant experiences an adverse event after the informed consent document is signed (entry) but the participant has not started to receive any study intervention, the event will be reported as not related to the study drug [13]. All adverse events occurring after entry into the trial and until the 90th day will be recorded. An adverse event that meets the criteria for a serious adverse event (SAE) between study enrollment and the 90th day will be reported to both the ethics committee of the hospital, and the Ethics Committee of Dongzhimen Hospital, Beijing University of Chinese Medicine as an SAE. A serious adverse event for this trial is any untoward medical occurrence that is believed by the investigators to be causally related to study drug and results in any of the following: after receiving the study drug, the participants need to be hospitalized, need to prolong the length of hospital stay, become disabled, be life threatened or dead, have congenital malformation, and other events. Investigators will evaluate the causal relationship between adverse events and study drugs.

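### Safety is analysed by intention to treat with adverse events counted from consent, which pulls the all-cause adverse event comparison toward no difference

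*Protocol article*

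**What the plan says.** Section {20a} says that "adverse events, serious adverse events, and laboratory abnormalities will also be compared using the chi-square test or Fisher exact test as appropriate". The next paragraph fixes the population for everything: "All analyses will be performed in the intention-to-treat population". The article names no other analysis population.

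Section {22} sets the counting window. "Adverse events will begin to be collected after the participant has provided consent and enrolled in the trial", and "All adverse events occurring after entry into the trial and until the 90th day will be recorded". Neither limit is tied to the first or last dose. The section foresees events after consent but before any study drug and says of these that "the event will be reported as not related to the study drug". It defines an SAE as an event judged causally related to study drug and arising after study drug was received.

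Randomisation follows consent (section {16a}). For participants who leave the trial, section {11b} states: "The participant’s data that have been collected up to that moment will be included in the analysis". Table 1 schedules AE and SAE recording from D0, but bleeding events and the post-baseline liver, kidney and coagulation tests only from D14.

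**The concern.** Intention to treat protects an efficacy comparison because non-exposure pulls the estimate toward no effect. In a harm comparison the same pull is the unsafe direction, because it can hide an excess caused by the added drug. Safety is half of the stated objective, and the Discussion hopes that lumbrokinase will bring no increase in haemorrhagic events.

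Two features of the stated rule act this way. A randomised participant who never takes study drug cannot have a drug-caused event but remains in the denominator. An event between consent and first dose cannot be caused by the drug but is counted as an AE, at the same expected rate in both arms.

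This is more than a detail left to a statistical analysis plan. The protocol states the population for all analyses, so a plan that used a treated set for safety would depart from the protocol's own wording.

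**Working it through.** **Inputs.** From the article: 110 participants per arm (section {14}), two-sided 5% level, Fisher or chi-square test on proportions (section {20a}). The article gives no AE rate, never-dosed share or pre-dose event rate, so there is no stated safety figure to reproduce. I assume true on-drug risks of 10% (lumbrokinase, p1) and 3% (control, p0). The true risk difference is 7 points, the risk ratio is 0.10/0.03 = 3.33, and exact Fisher power in the direction of harm is 47.5% at 110 per arm.

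**1. Never-dosed participants.** Let a share f of each arm never take study drug, with never-dosed lumbrokinase participants at control risk. The intention-to-treat risk in that arm is p1(1 − f) + p0·f, so the risk difference becomes (1 − f)(p1 − p0). The fair comparison is with the treated set that could actually be analysed, which has about 110(1 − f) per arm.

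| f | Risk difference, ITT | Power, ITT | Power, treated set |
|---|---|---|---|
| 2% | 0.98 × 7 = 6.9 points | 46.0% | 46.5% |
| 5% | 0.95 × 7 = 6.7 points | 43.9% | 44.5% |
| 10% | 0.90 × 7 = 6.3 points | 40.2% | 41.8% |

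The loss is 0.5 to 1.6 power points. With assumed risks of 15% and 5%, an approximate two-proportion calculation gives 68.4% against 68.9% (f = 2%), 66.3% against 67.6% (5%) and 62.6% against 65.2% (10%), a loss of 0.5 to 2.6 points. For commoner events (35% against 20%) the loss at f = 10% is 3.9 points (62.0% against 65.9%).

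**2. Pre-dose events.** Let b be the risk of any AE between consent and first dose, equal in both arms. The counted all-cause risk is 1 − (1 − b)(1 − p). The risk difference again shrinks by the factor (1 − b), but the added background lowers the ratio and the power much more.

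| b | Control | Lumbrokinase | Risk ratio | Fisher power |
|---|---|---|---|---|
| 0 | 3.0% | 10.0% | 3.33 | 47.5% |
| 2% | 1 − 0.98 × 0.97 = 4.9% | 1 − 0.98 × 0.90 = 11.8% | 2.39 | 36.8% |
| 5% | 1 − 0.95 × 0.97 = 7.9% | 1 − 0.95 × 0.90 = 14.5% | 1.85 | 27.8% |
| 10% | 1 − 0.90 × 0.97 = 12.7% | 1 − 0.90 × 0.90 = 19.0% | 1.50 | 19.5% |

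With 15% and 5% the risk ratio falls from 3.00 to 2.42, 1.97 and 1.62 for the same values of b.

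**3. Which outcomes each feature reaches.**
- All-cause AEs: both features.
- SAEs: never-dosed dilution only, because the definition requires the event to follow study drug.
- Bleeding and most post-baseline laboratory tests: never-dosed dilution, and hardly any pre-dose counting, because they are scheduled from D14.

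**4. Early leavers.** A participant who takes a dose and leaves event-free on day 7 counts as one event-free person in the intention-to-treat population and equally in a treated set. Per person-time, the same participant contributes 7 of 90 days. Only the second measure reflects the short observation.

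**The case against.** The strongest reply is that the effect is small and the text already guards against much of it. Pre-dose AEs are labelled unrelated, SAEs must follow study drug, and patients who cannot take drugs by mouth are excluded, so few never-dosed participants are likely. Most of this stands and limits the point. It does not remove it: the comparison is of adverse events without restriction to related ones, so labelling a pre-dose event as unrelated does not take it out of the all-cause count. The length of the gap between consent and first dose is not stated. If it is short, the lower end of the pre-dose range is the more plausible.

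The detailed definition of a treatment-emergent event can also fairly be left to the analysis plan. The population cannot, because the protocol has already fixed it.

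A reader might infer more than the documents support:
- **That intention to treat dilutes harm through early stopping.** Anyone with at least one dose is also in a treated set, and AE recording runs to day 90 whatever the drug intake. Short observation is a matter of using simple proportions, not of the population.
- **That stopping because of a side effect hides harm in the lumbrokinase arm.** That participant's event is already recorded and is in the numerator.
- **That the margin from 173 to 220 (1 − 173/220 = 21.4%) is the unexposed share, so that power falls from 47% to 32%.** Section {14} describes this margin as covering protocol violations and dropouts. The 47% also assumes 110 fully exposed participants per arm, which no analysis set would deliver. Even at 21.4% never dosed, intention to treat gives 32.0% against 34.7% in the treated set.
- **That any excess harm is diluted to the same degree.** Step 3 of the working shows otherwise.

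**Conclusion.** The point holds in a limited form. The protocol's stated rule keeps never-dosed participants in every safety denominator and puts pre-dose events into the all-cause AE numerators, and both act toward no difference.

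The never-dosed part is minor: the risk difference shrinks by the never-dosed share, at a cost of about 0.5 to 3 power points against an achievable treated set for most of the assumed rates. The pre-dose part is larger, but only for all-cause AEs: a risk ratio of 3.33 falls to between 2.39 and 1.50 for a pre-dose risk of 2% to 10%.

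The direction follows from the text. The sizes rest on assumed rates, on equal never-dosed and pre-dose rates in both arms, and on never-dosed participants having control risk. The change is worth making because it is standard and nearly free, not because the loss is known to be large.

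**What to change.** Keep intention to treat for the mRS and the other efficacy outcomes. In section {20a}, state that the main analysis of AEs, SAEs, bleeding events and laboratory abnormalities uses all randomised participants who took at least one dose of study drug, and counts events starting on or after the first dose. List pre-dose events separately by arm, and give the intention-to-treat safety table as a supplement. Since a change of population does nothing for early leavers, also report event rates per person-time observed.

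The cost is a second analysis population and an extra set of safety tables. Study drug is already counted at each follow-up visit (section {11c}), although the date of first dose must be available for each participant. Treatment and visits do not change. No interim analysis is planned and the data are analysed blind after database lock (section {18a}), so the wording can be settled before any comparison by arm is seen.

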### Outcomes {12}

The primary outcome is the Modified Rankin Scale (mRS) score.

The secondary outcomes are National Institutes of Health Stroke Scale (NIHSS) score, Activity of Daily Living (ADL) Scale score (Barthel index), coagulation function: prothrombin time (PT), activated partial thromboplastin time (APTT), serum fibrinogen (FIB) concentration, and serum hypersensitive C-reactive protein (hs-CRP).

The safety outcomes are liver function and kidney function: alanine aminotransferase (ALT), aspartate aminotransferase (AST), total bilirubin (TBil), blood urea nitrogen (BUN), serum creatinine (Scr), and urine protein (R-PRO), as well as serum fibrinogen (FIB), occurrence of adverse events (AEs) and serious adverse events (SAEs), and occurrence of bleeding events. Adherence of participants will also be assessed.

The exploratory outcomes include fasting lipid panel: total cholesterol (TC), triglyceride (TG), high-density lipoprotein (HDL), low-density lipoprotein (LDL), and recurrence rate (incidence of ischemic stroke events), occurrence of cardiovascular and cerebrovascular events, and mortality rate. A study schedule and evaluation of outcomes are provided in Table 1.

The five elements of the primary outcome and secondary outcomes are specified in Table 2: the domain, specific measurement, specific metric, method of aggregation, and time point.

**Table 2 Tab2:** Five elements of outcomes

	Domain	Specific measurement	Specific metric	Method of aggregation	Time point
Primary outcome	The Modified Rankin Scale (mRS) score	The Modified Rankin Scale (mRS) score	Change from baseline to 14, 28, 60, 90, and 180 days	Proportional-odds logistic-regression model	Baseline, 14, 28, 60, 90, and 180 days
Secondary outcome	National Institutes of Health Stroke Scale (NIHSS) score	National Institutes of Health Stroke Scale (NIHSS) score	Change from screening period to 14, 28, 60, and 90 days	Repeated-measures analysis model	Screening period, 14, 28, 60, and 90 days
	Activity of Daily Living (ADL) Scale score (Barthel index)	Activity of Daily Living (ADL) Scale score (Barthel index)	Change from baseline to 90 and 180 days	Repeated-measures analysis model	Baseline, 90 and 180 days
	Prothrombin time (PT)	Prothrombin time (PT)	Change from baseline to 14, 28, 60, and 90 days	Repeated-measures analysis model	Baseline, 14, 28, 60, and 90 days

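### The primary mRS outcome is listed at five visits with none singled out, while the sample size rests on day 90 alone; tested visit by visit without adjustment, its error rate would exceed 5%

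*Protocol article*

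**What the plan says.** Objectives {7} and Outcomes {12} name the primary outcome without a time: "The primary outcome is the Modified Rankin Scale (mRS) score". Outcomes {12} then says that Table 2 sets out the elements of each primary and secondary outcome, time point included. The primary row of that table reads "Change from baseline to 14, 28, 60, 90, and 180 days", and its aggregation method is a proportional-odds logistic-regression model. Days 14, 28, 60, 90 and 180 have equal standing there.

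Sample size {14} uses one visit only. It begins "A sample size of 173 participants was calculated to provide 80% power to detect a common odds ratio" and places the effect "in the distribution of scores on the mRS at 90 days", at a two-sided level of 0.05.

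Statistical methods {20a} says "The primary outcome will be analyzed by fitting a proportional-odds logistic-regression model to calculate the common odds ratio", again with no visit named. A different approach is kept for the secondary outcomes: "Longitudinal continuous variables will be analyzed by fitting a repeated-measures analysis model". For all analyses together, P "values of less than 0.05 will be considered statistical significance, and all tests will be two-sided", followed by "No adjustments will be made for multiple comparisons". Interim analyses {21b} plans none, so no part of the 5% is allocated elsewhere. No section gives a testing order, a gatekeeping rule or a joint test across visits.

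**The concern.** A confirmatory trial needs one stated rule for success on its primary outcome. Here the section that powers the trial implies one test at day 90, while the table that defines the outcome lists five post-baseline visits. The method named for the primary outcome yields one common odds ratio per fit and has no stated term for repeated visits. Taken with Table 2, the natural reading is one fit per visit, each judged at 0.05.

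Two things are at stake. First, if any visit may carry the claim, the false-positive rate for the primary outcome is above the stated 5%. Second, the plan has no answer when visits disagree, for example day 28 positive and day 90 null. The visits also answer different questions: days 14 to 60 fall within treatment, day 90 is its end, and day 180 follows 90 days on aspirin alone.

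**Working it through.** **Inputs from the protocol article**
- Post-baseline times in the primary row of Table 2: 14, 28, 60, 90 and 180 days, so k = 5.
- Level: two-sided 0.05 for every test, unadjusted ({20a}).
- Design test: one, at day 90, 80% power, common odds ratio 6.02, N = 173 before losses ({14}).
- Correlation between visits: not given, so a range is assumed.

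**The plan's own figures.** The 5% level holds exactly for what {14} describes, a single two-sided 0.05 test at day 90.

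The figure of 173 was not reproduced. The Whitehead formula is N = 12(z₀.₉₇₅ + z₀.₈₀)² / [(ln OR)²(1 − Σp̄³)], where p̄ is the mean proportion in each mRS category. With OR 6.02, 12 × 7.849 / 3.222 ≈ 29.2. Dividing by (1 − Σp̄³) gives about 30 to 51 in total over assumed seven-category distributions without extreme concentration. It comes near 173 (about 175) only if about 90% of controls are in the best category. This is a separate matter and does not affect the multiplicity question.

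**Five tests, any one counting as success, no effect at any visit**

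Upper bound: 5 × 0.05 = 25%.

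Independent tests: 1 − 0.95⁵ = 1 − 0.7738 = 22.6%.

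Scores from the same patients are positively correlated, so the true rate is lower. Five test statistics were simulated as multivariate normal (2 million draws), and the error rate taken as P(max|Z| > 1.960):

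| Assumed correlation | Equal between all visits | AR(1), value for adjacent visits |
|---|---|---|
| 0.5 | 18.3% | 20.1% |
| 0.8 | 12.7% | 14.9% |
| 0.9 | 10.2% | 11.8% |
| 0.95 | 8.5% | 9.7% |

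The rate is above 5% at every correlation tried.

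**Two ways to restore 5%**
- One named visit (day 90): the error rate is 5% and N is unchanged.
- Bonferroni, 0.01 per visit: the error rate is at most 5% (4.9% with independent tests). The sample grows by (2.576 + 0.842)² / (1.960 + 0.842)² = 11.68 / 7.85 = 1.49, which takes the plan's 173 to 257.4, so 258 before losses. Without more patients, power at each visit falls from 80% to Φ(1.960 + 0.842 − 2.576) = Φ(0.226) ≈ 59%.

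**The case against.** The best defence is that one day-90 test was always meant. Statistical methods {20a} describes a single model and a single common odds ratio, and {14} ties that same quantity to day 90. Table 2 can be read as a measurement schedule: its time-point column also lists baseline and mirrors the visit grid of Table 1. On that reading the no-adjustment sentence is unobjectionable, since it closes a paragraph that also covers secondary outcomes and safety.

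Part of this stands. A reader might infer that the protocol prescribes five separate primary tests with success on any one. No section says so, and the error rates apply only on that reading. But a sample-size assumption does not define an endpoint, and Table 2, which is presented as the definition, gives day 90 no special place. If one joint model over all visits was meant, it would in general estimate something other than the day-90 effect that {14} powers, so the sections would still need reconciling.

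It may also be said that the full analysis plan, not shown here, settles the matter. The article does not leave the time point open, however. It states five. A plan that took day 90 alone would depart from Table 2, and one that followed Table 2 and {20a} would keep five unadjusted comparisons.

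Blinding is a fair point too. Under {17a} and {18a}, analysts are blinded, analysis starts after database lock, and the code is opened once analysis is complete. This limits selection of a favourable visit but does not remove it, because coded groups can still be compared visit by visit.

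Finally, a reader might add the visits of the six secondary outcomes (4 + 2 + 4 + 4 + 4 + 1 = 19) to the five primary ones and speak of 24 unadjusted tests. The documents do not support that count. Table 2 assigns the secondary outcomes a repeated-measures model, and no section specifies a test at each visit. Leaving secondary outcomes unadjusted is common practice and is not the issue here.

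**Conclusion.** The point holds as an inconsistency with a conditional consequence. Table 2 defines the primary outcome at five visits and {14} powers one of them. The objectives, outcomes text and analysis section name none, and {20a} rules out adjustment. The decisive visit is therefore not fixed, and there is no verdict for discordant visits.

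If each visit were tested at 0.05 and any one taken as success, the family-wise error for the primary outcome would be about 8% to 20% for assumed between-visit correlations of 0.95 down to 0.5. That range rests on assumed correlations and on a success rule that the documents do not state. If day 90 is the only primary test, the error rate is 5% and nothing is inflated. The matter should be settled before unblinding, because it determines what counts as a positive trial.

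**What to change.** State in Objectives {7}, Outcomes {12} including Table 2, and Statistical methods {20a} that the single primary endpoint is the distribution of mRS scores at day 90, tested once at two-sided 0.05 with the proportional-odds model. Move mRS at days 14, 28, 60 and 180 to secondary or supportive outcomes, reported with confidence intervals and carrying no claim of primary success. The primary row of Table 2 should then describe the day-90 score distribution, as {14} does, in place of changes to five visits. The no-adjustment sentence can stay, since it would then concern only non-primary comparisons.

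The cost is an amendment to protocol and analysis-plan wording before unblinding. No new data are needed, the planned sample size stays as it is, and no power is lost at day 90.

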### Interim analyses {21b}

There are no interim analyses planned.

### Methods for additional analyses (e.g., subgroup analyses) {20b}

There are no subgroup analyses planned.

### Methods in analysis to handle protocol non-adherence and any statistical methods to handle missing data {20c}

The primary outcome will be assessed using an intention-to-treat analysis. Missing data will be reduced to a minimum by using the appropriate measures described above. If any statistical method is needed to account for missing data in the secondary outcomes, multiple imputation will be used.

### Plans to give access to the full protocol, participant-level data, and statistical code {31c}

The data sets generated and/or analyzed during the current study are not publicly available, owing to the protection of privacy for participants, but they are available from the corresponding author on reasonable request.

